# Evaluation of the Effectiveness of an Osseodensification System for Improvement in Bone Density After Delayed Implant Placement: Protocol for a Single-Arm Pilot Study

**DOI:** 10.2196/80200

**Published:** 2026-09-01

**Keywords:** osseodensification, dental implants, bone density, implant stability quotient, ISQ, Hounsfield units, HU, delayed implant placement, bone-to-implant contact, BIC, resonance frequency analysis, RFA, pilot clinical study, osseointegration

## Abstract

**Background:**

Delayed placement of dental implants often leads to bone resorption, particularly in the posterior region, compromising implant placement. Osseodensification uses specialized rotary instruments to compact and densify bone and may improve bone quality and implant stability. However, its effectiveness in delayed implant placement has not been fully explored.

**Objective:**

This study aims to assess the effectiveness of osseodensification in increasing bone volume and density at regions scheduled for delayed implant placement and to evaluate its effect on implant stability and osseointegration.

**Methods:**

This 9-month single-arm clinical and radiographic study will include 22 systemically healthy patients with D2-D3 bone quality in an edentulous region of the anterior or posterior arch. Preoperative full-mouth ultrasonic scaling, dental hygiene instructions, and cone beam computed tomography (CBCT) imaging will be performed. Bone density will be measured at the coronal (mesial and distal), middle and apical regions of the extraction socket in Hounsfield Units (MU). During implant placement, osseodensification will be used for osteotomy preparation. Implant Stability Quotient (ISQ) values will be assessed using resonance frequency analysis. CBCT imaging will be done at baseline, 3 months, and 9 months post surgery. Recruitment began in July 2025 following ethics approval and trial registration (CTRI/2025/03/082513). The primary outcomes include changes in bone density and implant stability; secondary outcomes assess peri-implant bone healing, osseointegration, and complications.

**Results:**

Recruitment began in July 2025, and as of October 2025, screening and baseline assessments are ongoing. Enrolment of 22 participants was expected by January 2026, with the surgical phase expected to be completed by April 2026. Follow-up evaluations will be performed at baseline, 3 months, and 9 months post surgery. Final data collection and statistical analysis are anticipated by July 2026. No outcome data are yet available because the study is ongoing.

**Conclusions:**

This ongoing pilot study will provide preliminary evidence on the feasibility of osseodensification for delayed implant placement and its effect on bone density and implant stability. The findings may guide methodological refinements and future controlled clinical trials.

**Trial Registration:**

Clinical Trials Registry India CTRI/2025/03/082513; https://tinyurl.com/34562c7b

**International Registered Report Identifier (IRRID):**

PRR1-10.2196/80200

## Introduction

Dental implant placement is a cornerstone procedure in modern dentistry, offering a long-term solution for patients with missing or damaged teeth. Dental implant placement faces challenges such as insufficient bone density, which may require grafting, and risks like infection, poor osseointegration, or mechanical failure [1]. Nevertheless, we must consider that even in healthy individuals and experienced operators, some implant complications (peri-implantitis, bone dehiscence, and impossibility to obtain ideal implant stability) may be a very common situation because of other etiologic agents, such as biomechanical factors or inadequate preparation of the site hosting the implant [2,3]. The presence of systemic diseases (diabetes mellitus, coagulation disorders, and osteoporosis), anticoagulant, bisphosphonate, and aspirin therapy [4], as well as the physiology and anatomy of the treated structure (bone quantity and density and mental nerve not far from the level of the bone crest) could all affect the outcome of the treatment. Other factors depend on the operator (experience, methods, instruments used, and team skills).

Due to decreased bone quality and primary stability, patients with low bone density, such as those with managed osteoporosis, mild to moderate bone loss, especially in the posterior maxilla, older patients, or those receiving long-term steroid therapy (but not high-risk medications like long-term intravenous bisphosphonates), present challenging situations for implant therapy [5,6]. Patients with lower bone density are at increased risk for both primary and secondary implant failure. Primary failure refers to the inability of the implant to integrate correctly with the bone during the healing phase, usually caused by inadequate support from the bone or poor osseointegration. Secondary failure can occur after a period, usually due to complications like peri-implantitis or mechanical overload, which may be more likely in patients with compromised bone density [6-8]. Insufficient bone volume or quality may compromise the initial stability of the implant, increasing the risk of these failures. Such problems necessitate bone-based grafting or sinus lift intervention, but even after these interventions, the risk is still relatively higher for implant failure in such patients with low bone density [9]. The outcome of implant therapy is greatly influenced by bone density, which is frequently categorized as D1, D2, D3, and D4 according to its quality and structure. While D2 bone, which is medium dense and primarily trabecular with a cortical shell, is thought to be the most suitable for implant placement because of its balance of density and vascularity, D1 bone is dense and cortical, providing great primary stability. On the other hand, D4 is the least supportive of the D3 and D4 bones, which are becoming less dense and more porous. Although successful osseointegration requires meticulous expertise, implants put in D2 bone typically have positive results [10].

Different issues may arise when placing implants in D2, where the bone is of medium density, and in D3, where the bone is poor in quality. Dental implants placed in D2 type bone are likely to have enough support, although their placement needs careful attention for good osseointegration. D3 bone, on the other hand, is of lower density and more porous [11]. The primary stability may be poor and the risk of implant failure increases. To counter these difficulties, a bone grafting procedure or a larger or special design of implants may be needed. Implants in D3 bone have a higher risk of complications such as failure of osseointegration or implant loosening, requiring close monitoring during the healing process [12].

Subtractive drilling, which is used in traditional osteotomy preparation for implant placement, removes bone and may further lower density at the implant site, impairing insertion torque and delaying osseointegration [13]. In order to overcome these limitations, osseodensification, first presented by Huwais and Meyer [14] in 2013 was developed as a biomechanical drilling method that preserves and densifies native bone by compacting and autografting bone along the osteotomy walls. Osseodensification increases mechanical stability and improves the bone-to-implant contact (BIC) surface by rotating specifically made burs counterclockwise and without cutting [5]. This method densifies bone along the osteotomy walls by rotating specially made burs counterclockwise [14]. Numerous benefits have been documented by studies, such as enhanced BIC, quicker healing, and better primary stability. It involves the use of specifically designed drills that expand the osteotomy site and compact the surrounding bone, thus preserving it. The key advantages of osseodensification include improved primary stability, especially in cases with lower bone density, and enhanced bone quality around the implant. This technique has shown potential to reduce the need for bone grafting procedures [15,16], promote better osseointegration, and improve overall implant success rates. However, it requires skill and experience to avoid over compaction or potential damage to the bone.

Despite these positive outcomes, the majority of the data is derived from retrospective analyses using diverse methodologies, animal models, or in vitro research. Only a few well-designed prospective clinical trials have evaluated osseodensification for delayed implant placement in moderate-density bone, especially when using stability measures and standardized radiography over an extended period of time [6,8]. Therefore, controlled studies that methodically assess the effects of osseodensification on bone density, primary stability, and osseointegration in vivo are required.

Despite the growing evidence supporting osseodensification, most available studies are retrospective, based on animal or in vitro models, or involve heterogeneous methodologies and follow-up periods. Only a limited number of well-designed prospective studies have evaluated osseodensification specifically for delayed implant placement in moderate-density bone (D2-D3) using standardized radiographic parameters and implant stability measurements over time [6,8]. However, these studies often differ in measurement protocols, timing of evaluations, and implant systems used, making it difficult to compare outcomes or establish clear clinical guidelines.

Therefore, before undertaking large-scale controlled trials, it is necessary to conduct a feasibility-oriented pilot study to assess the practicality, reproducibility, and short-term clinical outcomes of osseodensification under standardized conditions. The present single-arm exploratory study was designed to address this need. By applying uniform cone beam computed tomography (CBCT)–based bone density assessments (in Hounsfield Units [HU]) and resonance frequency analysis (Implant Stability Quotient [ISQ]) at defined intervals, this study aims to generate preliminary clinical data on how osseodensification influences bone density and implant stability in delayed implant sites.

Unlike prior retrospective or ex vivo investigations, this protocol emphasizes methodological standardization and longitudinal follow-up within a real clinical setting. The findings will serve as baseline data for estimating effect sizes, refining study logistics, and informing the design of future randomized controlled trials that can definitively compare osseodensification with conventional osteotomy techniques.

This study will help to bridge the evidence gap and offer recommendations regarding whether osseodensification can be a practical substitute for traditional drilling methods in improving the success of dental implants through clinical and radiographic assessments [17]. Thus, this study aims to assess how well osseodensification works to increase bone density and implant durability in delayed implant implantation within bone quality sites D2 and D3. Changes in peri-implant bone density, insertion torque, and implant stability over time will be evaluated using clinical and radiographic studies.

## Methods

### Overview

This single-arm study will aim at assessing the efficiency of the osseodensification system in enhancing the bone density and volume in cases with delayed implant placement. It will assess the osseodensification impact on the healing of bones and osseointegration, which is by comparing the clinical and radiographic outcomes before surgery and after it.

### Ethical Considerations

This study protocol was reviewed and approved by the Institutional Ethics Committee (IEC), Datta Meghe Institute of Higher Education and Research (deemed to be university [DU]), Wardha, Maharashtra, India (approval number DMIHER(DU)/IEC/2025/561). The study has also been registered with the Clinical Trials Registry of India (CTRI) under the registration number CTRI/2025/03/082513.

Written informed consent will be obtained before any subject is recruited. Through an information sheet and a verbal explanation from the researchers, each participant will receive comprehensive information on the study's goals, methods, potential risks, and anticipated advantages. No personally identifiable information will be revealed in study reports or publications, and confidentiality will be preserved by issuing unique identifying codes. At any point during the study, participants will have the liberty to leave without affecting their ongoing or future treatments.

### Sample Size Calculation

Based on the key outcome variable, implant stability (ISQ values), which will be evaluated at baseline, 3 months, and 9 months post surgery in the same patients, the sample size for this study was estimated. The repeated measures ANOVA framework was chosen because it takes into consideration correlations between several observations made on the same subject.

According to earlier research assessing osseodensification, the average ISQ improvements were between 3 and 5 units, with SDs varying between 1.5 and 2.5. For repeated measures over three time points, a modest effect size (f=0.40) was anticipated using these estimations. The necessary sample size was determined to be 22 patients with α=.05, power=0.90, and correlation among repeated measurements set at 0.5 (G*Power 3.1; Heinrich Heine University Düsseldorf; repeated measures ANOVA, within-subject variables).[18]

This sample size will guarantee feasibility in the framework of an exploratory clinical protocol and offer enough power to identify clinically significant variations in bone density and implant stability over the course of the trial.

The calculation used the formula stated below, where the input parameters are as follows:

The input parameters are α (for a 95% CI)=1.96, : 0.01 (power=1β=99%)=2.57, and mean difference 4 (SD 1.86).

The minimum paired sample size needed is 22 participants.

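### The sample size section supports N=22 with two incompatible calculations, and neither gives 22 from its listed inputs

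*Protocol article*

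**What the plan says.** All of this stands in the protocol article, Methods, Sample Size Calculation.

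- The size is based on ISQ, "which will be evaluated at baseline, 3 months, and 9 months post surgery in the same patients". Earlier work is cited for ISQ gains of 3 to 5 units with SDs of 1.5 to 2.5.
- From these the section takes its effect size: "For repeated measures over three time points, a modest effect size (f=0.40) was anticipated using these estimations".
- The first result, attributed to the G*Power within-subject ANOVA, is "The necessary sample size was determined to be 22 patients with α=.05, power=0.90, and correlation among repeated measurements set at 0.5".
- The section then says that the calculation used a formula whose inputs are 1.96 for alpha and, for the rest, "0.01 (power=1β=99%)=2.57, and mean difference 4 (SD 1.86". It closes with "The minimum paired sample size needed is 22 participants".
- It also says that this number will "offer enough power to identify clinically significant variations in bone density and implant stability".

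The Statistical Analysis section plans a repeated measures ANOVA for ISQ and bone density, with a Greenhouse-Geisser correction if sphericity fails. It prefers this to paired t tests because there are three time points.

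**The concern.** One N is given as the result of two calculations that share almost nothing: an F test over three time points at 90% power, and a paired comparison at 99% power for a 4-unit difference. A reader cannot tell which one sized the trial. The second is of a kind that the Statistical Analysis section sets aside. Neither result looked reproducible, the multiplier 2.57 looked wrong for 99% power, and f=0.40 looked small beside the ISQ changes said to produce it.

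What is at stake is traceability. The Introduction and Expected Outcomes sections say the study is meant to supply effect sizes for later randomised trials. Those who design such trials will look to this section for the assumed effect, correlation and power, and at present these cannot be relied on. The claim about power for bone density, a primary outcome, also goes beyond what was calculated.

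**Working it through.** **Calculation A: repeated measures ANOVA.** Stated inputs: f=0.40, alpha 0.05, power 0.90, correlation rho=0.5, m=3 time points, one group. Nonsphericity epsilon and dropout are not stated, so the base case takes epsilon=1 and no dropout.

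Noncentrality: lambda = f² × N × m × epsilon / (1 − rho) = 0.16 × 3 / 0.5 × N = 0.96N, with (m−1)epsilon and (N−1)(m−1)epsilon degrees of freedom.

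| N | lambda | df | Power |
|---|---|---|---|
| 14 | 13.44 | 2, 26 | 0.882 |
| 15 | 14.40 | 2, 28 | 0.906 |
| 22 | 21.12 | 2, 42 | 0.984 |

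The required N is 15, against 22 stated. What would produce 22:

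| Change to A | N for 90% power | Power at 22 |
|---|---|---|
| epsilon=0.75 | 18 | 0.953 |
| epsilon=0.6 | 22 | 0.914 |
| epsilon=0.5 (lower bound for three time points) | 24 | 0.872 |
| 30% dropout added to 15 | 15/0.70 = 21.4, so 22 | – |
| rho=0.25 | 22 | – |

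Epsilon and dropout are not stated, and rho=0.25 contradicts the stated 0.5. At 99% power with epsilon=1, A needs 24, so A does not give 22 at that power either.

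**Calculation B: paired formula.** Stated inputs: 1.96, 2.57, difference 4, SD 1.86. The formula is not visible in the text reviewed, so the standard forms are used.

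- Paired: n = (1.96 + 2.57)² × 1.86² / 4² = 20.52 × 3.460 / 16 = 4.44, so 5. The exact t calculation for 99% power gives 7.
- With the two-group factor 2: 8.87, so 9 per arm, or 18 in total.
- To return 22, the paired form would need an SD of 4 × √22 / 4.53 = 4.14, or a difference of 1.86 × 4.53 / √22 = 1.80.

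**The multiplier.** z(0.99) = 2.326 and z(0.995) = 2.576. The printed 2.57 corresponds to about 99.5% power. With 2.326 the paired form gives 3.97, so 4.

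**The effect size.** At rho=0.5 the SD of a change is SD × √(2 × 0.5), which equals the SD at one time point, so it does not matter which of the two the cited SDs are. For a given largest change d over three means, even spacing (0, d/2, d) gives the smallest f = d / (√6 × SD):

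- 3 units, SD 2.5: 0.49
- 4 units, SD 1.86: 0.88
- 5 units, SD 1.5: 1.36

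If the whole change occurs by the second time point (0, d, d), the range is 0.57 to 1.57. No stated combination gives 0.40.

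**Bone density.** No Hounsfield unit difference or SD enters A or B.

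**Precision at N=22.** The 95% CI half-width for mean ISQ change is t(21) × SD / √22 = 2.080 × 1.86 / 4.690 = 0.82 units. It is 0.67 for SD 1.5 and 1.11 for SD 2.5.

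**The case against.** The strongest defence is that the answer of 15 is conditional. The Statistical Analysis section foresees nonsphericity, an epsilon of about 0.6 gives exactly 22, and a condensed article may leave epsilon or attrition to the full protocol. This stands as far as it goes: A should be called not reproducible from its listed inputs, not impossible. It does not help B, nor does it reconcile 90% with 99% power.

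The formula for B cannot be seen, so a non-standard form cannot be excluded. Both standard forms nevertheless miss 22 by a wide margin when 22 is read, as the section words it, as a number of pairs.

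On f, every value implied by the cited changes exceeds 0.40, so the choice is conservative. That also stands. What remains is that the section presents it as obtained from those figures: "a modest effect size (f=0.40) was anticipated using these estimations".

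On bone density, f has no units, so A covers any outcome with f=0.40 and rho=0.5. It would therefore go too far to say that the claim can have no basis. The fair point is that nothing stated shows this f to be plausible for Hounsfield units.

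A reader might infer from irreproducible arithmetic that the trial is underpowered. The documents do not support this for ISQ: 22 exceeds what A needs at epsilon=1 and what B needs, and under A's inputs power at 22 is still 87% at the lowest possible epsilon.

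**Conclusion.** The point holds as an error of justification. The section attributes N=22 to two incompatible calculations. On the listed inputs A needs 15 (epsilon=1, no dropout) and B about 5 (standard paired form). Power at 22 under A is 98%, not the stated 90%, unless epsilon is near 0.6. The z value given for 99% power is wrong whatever the formula. The assumed f=0.40 is below the smallest value, about 0.49, that the cited changes imply; it is cautious but not derived from them. Power for bone density is asserted without supporting data. None of this shows that 22 is too few for ISQ, and none of it calls for a different enrolment.

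**What to change.** Keep N=22 and rewrite the one section:

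1. Delete the paired calculation with its 99% power and 2.57.
2. Keep the ANOVA calculation, which matches the planned analysis. State epsilon and any dropout allowance, and report the power that follows: with 22 completers, 98% at epsilon=1, 91% at epsilon=0.6 or 87% at epsilon=0.5.
3. Describe f=0.40 as a conservative assumption that is smaller than the cited ISQ changes imply.
4. State that the size was based on ISQ and that power for bone density was not separately established.
5. Optionally, add the precision for mean ISQ change: a 95% CI half-width of 0.82 units at SD 1.86, and 0.67 to 1.11 for SDs of 1.5 to 2.5.

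The cost is a text correction. Enrolment, visits and the planned analysis stay as they are.

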### Eligibility Criteria

#### Inclusion Criteria

The inclusion criteria of this study appear to preferentially select patients who are most likely to achieve successful outcomes. Participants are required to demonstrate optimal oral hygiene (plaque score ≤25%), have a thick gingival biotype, intact alveolar bone walls, at least 4 mm of bone at the root apex, and favorable bone quality (D2 or D3). Additionally, an opposing natural tooth and stable adjacent teeth are necessary to ensure proper occlusal function. Patients are restricted to the 30- to 59-year age range. Since it improves soft tissue resilience and promotes superior cosmetic results, a thick gingival biotype is ideal. For adequate structural support, radiographic and clinical assessments must verify that the alveolar bone walls are intact. Additionally, in order to ensure sufficient bone availability, radiography should show at least 4 mm of bone at the root apex. Finally, because D2 or D3 bone quality promotes good osseointegration and implant stability, only these locations will be included.

#### Exclusion Criteria

The study’s exclusion criteria are intended to maximize treatment success, minimize potential problems, and guarantee the selection of qualified patients. To avoid negative reactions and associated difficulties, any individual with known sensitivities to titanium or other implant materials will not be accepted. In addition, patients with systemic illnesses that can impair healing and implant integration, such as diabetes or cardiovascular problems, will be excluded. Due to the higher risk of implant failure, those with active mouth infections or periodontal disease will not be eligible. To prevent any possible hazards to the health of the mother or fetus, women who are currently breastfeeding or pregnant will not be allowed to participate. In addition, due to their impaired healing ability and increased risk of implant failure, people who smoke or have a history of alcohol or drug abuse will not be considered.

This study will be carried out in the Outpatient Department of Periodontology and Implantology, Datta Meghe Institute of Higher Education and Research (DU), Wardha, Maharashtra, India, a teaching hospital for tertiary care dentistry that has a special implant therapy unit. The center was selected because it consistently receives patients requiring implant-supported rehabilitation and has the CBCT imaging and surgical capabilities needed for the study. Recruitment will be done in a methodical way: during routine consultations, consecutive patients who present with edentulous spaces suitable for delayed implant placement will be screened. Sites with D2 or D3 bone quality will be identified by reviewing their dental records and, if available, preliminary radiographs. After confirming basic eligibility by a quick chairside screening of medical history, age, and site features, a calibrated investigator will invite participants who meet these preliminary requirements for a more thorough assessment. Patients who exhibit good dental hygiene (plaque score <25%), intact alveolar walls, and enough bone height will be shortlisted after thorough clinical and radiographic tests, including periodontal charting and CBCT, verifying compliance with the inclusion and exclusion criteria. Before obtaining formal informed permission, the study’s goals, methods, possible dangers, and advantages will be thoroughly presented both orally and in a patient information sheet, giving sufficient time for questions. Participants who are eligible and give their consent will be listed in a recruitment log, given a special identification code, and scheduled for baseline procedures such as preoperative photos, diagnostic castings, and full-mouth ultrasonic scaling. Participants will get instruction on dental hygiene and the significance of attending follow-up appointments at three and nine months, and their contact information (phone number and email) will be recorded to facilitate appointment reminders. Under the principal investigator’s direction, all recruitment efforts will be carried out by qualified investigators following the guidelines of Good Clinical Practice.

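### As written, the CBCT that verifies trial eligibility comes before the study is explained and consent is taken, so people who fail on the scan or then decline are irradiated without study consent

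*Protocol article*

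**What the plan says.** The recruitment paragraph at the end of Exclusion Criteria describes a stepwise process. After a record review and a brief chairside check, "a calibrated investigator will invite participants who meet these preliminary requirements for a more thorough assessment". Patients with suitable hygiene, socket walls and bone height then "will be shortlisted after thorough clinical and radiographic tests, including periodontal charting and CBCT, verifying compliance with the inclusion and exclusion criteria". The next sentence reads "Before obtaining formal informed permission, the study’s goals, methods, possible dangers, and advantages will be thoroughly presented". After that, "Participants who are eligible and give their consent will be listed in a recruitment log, given a special identification code", and these people are "scheduled for baseline procedures such as preoperative photos, diagnostic castings, and full-mouth ultrasonic scaling".

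The general rule stands in Ethical Considerations: "Written informed consent will be obtained before any subject is recruited".

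**The concern.** A scan done to check a trial's entry criteria is a trial procedure and involves ionising radiation. Consent should come before it. In the order given, two groups are scanned for the trial without having agreed to take part: those whose CBCT shows that they do not qualify, and those who qualify but decline once the study is explained. What is at stake is the protection of these people, who gain nothing from the trial. There is also a gap in the record: the only log described holds people who are already eligible and consenting, so it would not show who was scanned and not enrolled.

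**Working it through.** No power or sample size calculation bears on this point. The check is to set the passages side by side.

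**Order in the recruitment paragraph**
1. Consecutive patients at routine consultations are screened from dental records and any radiographs that already exist.
2. A brief chairside check covers health history, age and the site.
3. Those who pass are invited to a fuller assessment. No study explanation or consent is mentioned here.
4. Periodontal charting and CBCT verify the inclusion and exclusion criteria, and patients are shortlisted.
5. The study is explained and formal consent obtained.
6. Eligible, consenting people are logged, coded and scheduled. Photographs, casts and scaling are named at this step; CBCT is not.

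**Purpose of the scan.** Step 4 gives it directly: checking the trial's criteria. The abstract's Methods list preoperative CBCT among the study procedures, and the recruitment paragraph counts CBCT among the capabilities that the study needs. Nowhere does the article describe this scan as routine care that would be done anyway.

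**Whether failures at step 4 are foreseeable.** Inclusion Criteria require intact alveolar walls, at least 4 mm of bone at the root apex and D2 or D3 quality. Before step 4 these are judged only from records and whatever radiographs are available. Some failures on CBCT must be expected.

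**Whether Ethical Considerations closes the gap.** It ties consent to recruitment, and there are two readings.
- Screening is part of recruitment. The recruitment paragraph introduces the whole sequence as the way recruitment is done. Consent must then precede step 4, and the two places conflict.
- Recruitment means enrolment after step 5. The places then agree, but no stated consent covers the scan at step 4.

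The text needs correcting on either reading.

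**Number affected.** If S people are scanned at step 4 and the target of 22 is enrolled, S − 22 were scanned without study consent. The article gives neither S nor any rate from which to derive it.

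**The case against.** The strongest reply is that the order is read from a narrative. No sentence says outright that consent follows CBCT, and "Before obtaining formal informed permission" fixes only that the explanation precedes consent. Ethical Considerations can be read as putting consent first, the recruitment paragraph commits to Good Clinical Practice, and an ethics committee approved the study. The list of procedures after consent is open-ended, so the absence of CBCT from it proves little. Patients come from routine consultations at a centre with an implant unit, where CBCT may also be ordinary planning. The article is a condensed account, and the consent documents are not shown. Finally, recruitment began in July 2025, enrolment was expected to be complete by January 2026 and the article is dated September 2026, so a reordered paragraph may not change how anyone was screened.

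Part of this stands. The complaint must be limited to study consent, since ordinary clinical consent for imaging is not discussed. If the scan is standard planning, the exposure is not caused by the trial; but the article does not say so, and the only purpose it gives at that step is checking trial criteria. The sequence is stated step by step, so this is more than detail left to a fuller document. If actual practice differs, the paragraph misdescribes it and still needs correcting.

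**Conclusion.** The point holds for the sequence as written: CBCT for trial eligibility comes before study information and consent, and this does not sit with Ethical Considerations. It rests on reading the paragraph in the order in which it is written, and on the absence of any statement that the scan is routine care. It does not establish that anyone was in fact scanned without consent.

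A reader might infer more than the article supports:
- *That the order biases the results because the investigator sees the bone findings before inviting consent.* Bone quality and wall status are inclusion criteria, so they must be seen before enrolment whenever consent is taken.
- *That the screening scan supplies the baseline bone density.* Radiographic Measurements describes a preoperative CBCT but does not say whether it is the same scan.
- *That pregnancy is first checked at the scan.* The article says that "women who are currently breastfeeding or pregnant will not be allowed to participate" without fixing when this is checked; the chairside history comes before the CBCT and may reveal it.
- *That everyone screened is exposed.* Only those invited after the chairside check reach the CBCT.
- *That a count of unconsented scans can be given.* Any figure would rest on a failure rate that the article does not supply.

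The change is worth making for participant protection. It does not affect the validity of the planned analysis.

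**What to change.** In the recruitment paragraph, place the study information and written consent directly after the chairside screen and before any CBCT done to verify trial eligibility. If the scan is standard implant planning, say instead that it is done regardless of the trial and used for the study only after consent. Word Ethical Considerations to match. Start the log at consent, so that people who consent and then fail screening are recorded with the reason. If enrolment is already complete, state which order was followed.

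The cost is one reordered paragraph, with no added procedure. The downside is that some people will consent and then fail screening.
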